## Abstract

**Background:**

Although this has not been fully studied, videos and pictorial brochures might be equivalent methods of delivering HIV/AIDS and HIV testing information to emergency departments (ED) patients. It also is not known how well or for how long such knowledge is retained, if this information should be tailored according to patient health literacy, and if retention of this knowledge impacts future HIV testing behavior.

**Methods:**

We will conduct a multi-site, randomized, controlled, longitudinal trial among 600 English- and 600 Spanish-speaking 18–64-year-old ED patients to investigate these questions. We will stratify our sample within language (English vs. Spanish) by health literacy level (lower vs. higher) and randomly assign patients to receive HIV/AIDS and HIV testing information by video or pictorial brochure. All patients will be tested for HIV in the ED. At 12-months post-enrollment, we will invite participants to be tested again for HIV. As primary aims, we will compare the efficacy of pictorial brochures and videos in improving short-term (in ED) HIV/AIDS and HIV testing knowledge and retaining this knowledge over 12 months. We will determine if and how short-term improvement and longer-term retention of knowledge interacts with information delivery mode (pictorial brochure or video), patient health literacy level (lower or higher), and language (English or Spanish). As secondary aims, using the Information-Motivation-Behavioral Skills (IMB) model as a heuristic framework, we will measure constructs from the IMB model relevant to our study, and assess their impact on HIV re-testing behavior; we will also examine the moderating influences of information delivery mode, language, and health literacy level. In addition, we will explore simplified screening strategies to identify ED patients with lower health literacy as ways to implement a tailored approach to HIV/AIDS and HIV testing information delivery in EDs.

**Discussion:**

Study findings will guide ED-based delivery of HIV/AIDS and HIV testing information; that is, whether delivery modes (video or pictorial brochure) should be selected for patients by language and/or health literacy level. The results also will inform EDs when, how, and for whom information needs to be provided for those undergoing testing again for HIV within a one-year period.

**Trial registration:**

ClinicalTrials.gov Identifier: NCT02284451. Posted November 6, 2014.

**Electronic supplementary material:**

The online version of this article (10.1186/s12873-018-0172-7) contains supplementary material, which is available to authorized users.

## Background

The United States (US) Centers for Disease Control and Prevention (CDC) recommends that all patients at every HIV testing encounter receive information orally or in writing about HIV/AIDS and HIV testing [1]. CDC recommends that this information includes the benefits and consequences of HIV testing, HIV transmission and prevention, testing methods/procedures, the meaning of possible test results, and how to find additional information for counseling and other services [2]. The primary intent of this information is to improve HIV/AIDS and HIV testing knowledge, although it likely also affects motivation and behavioral skills around HIV testing, HIV risk-taking behaviors, and future HIV testing utilization. However, no published research exists that indicates how, in what form, and how often this information should be delivered to improve and retain HIV/AIDS and HIV testing knowledge; if it is best delivered by the two CDC-recommended delivery modes (orally or in writing); if this information must be provided to all patients at every testing encounter; if and how it could be delivered according to patient needs and abilities (e.g., health literacy skills); or how this information and its delivery mode affects patients HIV testing motivation and skills, HIV risk-taking, and future HIV re-testing*.*

Oral information delivery is limited by variations in staff abilities, access to translators, and scarce resources. Evidence supporting the efficacy of written informational brochures in improving HIV/AIDS and HIV testing knowledge is scant*.* A 1986 study reported that only 40% of Swiss citizens receiving an informational brochure about HIV/AIDS read it entirely and 11% refused to read it, yet those who read it had greater HIV/AIDS knowledge 2 weeks later [3]. A United Kingdom sexually transmitted disease (STD) clinic study found that an informational pamphlet increased HIV testing knowledge similar to an in-person discussion for lower HIV risk clients [4]. However, written brochures might not be useful for those with lower health or general literacy, especially when in a text-only form [5–8]. A study of 136 HIV/AIDS written materials found that more than half were at a 10th–12th-grade reading comprehension level and 13% were at a university level [5]. As such, these materials are not useful for lower literacy patients. Of greater concern, a 1997 review of 72 state, federal, or privately-produced HIV/AIDS brochures concluded that approximately 95% contained inaccuracies so severe that their use was not recommended [9].

Having efficacious yet efficient modes of delivering HIV/AIDS and HIV testing information can remove a barrier to emergency department (ED) HIV testing. For EDs, videos might be a better alternative to oral and written HIV/AIDS and HIV testing information*.* They can be delivered at any time or location with fewer staffing requirements; can be provided to those awaiting services, making the testing encounter more efficient; and can be adapted for multiple languages, which helps reduce the need for in-person or telephonic translation services. Videos might be better than written brochures because they combine audio and visual imagery that can work together to enhance the effectiveness of delivering information [10, 11], especially for people with lower general literacy and lower health literacy [12, 13]. ED-based, video-delivered HIV/AIDS and HIV testing information has been promising. Calderon, et al. observed that ED patients watching a “pre-test” HIV informational video scored better on a 10-item knowledge questionnaire than those receiving information orally (∆ 5.6%; 90% CI 2.6–8.7%) [14]. In addition, adult ED patients watching a “post-test” video scored better than those in an oral information group (∆ 6.9%; 90% CI 2.8–11.2%) [15], as did pediatric/young adult ED patients (∆ 12.2%; 95% CI 3.2–16.5%) [16].

Our research group has conducted several studies examining delivery of HIV/AIDS and HIV testing information in EDs. In a 2005 pilot study, English-speaking, 18–55-year-old Rhode Island Hospital ED patients were randomly assigned to receive either no information or information delivered orally by an HIV test counselor (a research assistant [RA]) [17]. The topics for the orally-delivered information reflected CDC recommendations on HIV/AIDS and HIV testing information that HIV test recipients should receive when being tested for HIV [2, 18]. All study participants completed a 26-item questionnaire to measure their HIV/AIDS and HIV testing knowledge applicable to these CDC recommendations. Participants randomly assigned to the no information arm of the pilot study answered an average of 50% of the questions correctly, compared to an average of 77% who received information orally (*p* < 0.001). These results indicated a need for HIV/AIDS and HIV testing information for ED patients.

During 2004–2005, we produced a professional quality, animated and live-action, 9.5 min, English-language HIV/AIDS and HIV testing informational video, “Do you know about rapid HIV testing?” [17] During 2005–2006, we conducted a randomized, controlled, non-inferiority trial (K23AI060363) to determine if the video was as efficacious in improving HIV/AIDS and HIV testing knowledge as information delivered orally by an HIV test counselor (a RA) among ED patients before rapid HIV testing [19]. After receiving the information from the video or counselor, participants assigned to the video and the orally-delivered information arms had similar mean scores for correct items (20.1 vs. 20.8) on the 26-item HIV/AIDS and HIV testing knowledge questionnaire from the previous pilot study. Also, the majority (94%) of participants in both study arms believed they were “well” or “very well informed” by the information they received [20]. Yet, English-speaking Latino patients had lower mean scores than non-Latinos, regardless of watching the video or having received information orally. This difference persisted even when controlling for years of education.

In 2010, we began a second study (R21NR011997) to adapt our English-language video, “Do you know about HIV and HIV testing?” into a 15-min Spanish-language video, “¿Qué sabe usted sobre el VIH y sobre las pruebas del VIH?” through a rigorous multi-step process. We conducted two rounds of cognitive-based assessments and pilot testing of the video and accompanying HIV/AIDS and HIV testing knowledge questionnaire among 18–64-year-old Latinos (*n* = 120) at three non-clinical community-based organizations (Chicago, Miami, and San Antonio), and three clinical sites of an ambulatory medical clinic (Providence), an ED (Los Angeles), and a department of health clinic (San Juan). In addition, we conducted similar assessments among 30 bilingual (English- and Spanish-speaking) Latino HIV test providers at the respective community-based organizations. We revised the video based on the results of the cognitive-based assessments and the pilot testing. During this process, we also adapted and tested an accompanying 25-item questionnaire designed to assess HIV/AIDS and HIV testing knowledge applicable to the goals of providing CDC-recommended HIV/AIDS and HIV testing information at the time of HIV testing. We verified the utility of the questionnaire through pilot testing and cognitive-based assessments (Cronbach’s α = 0.80).

We employed the Spanish-language video and questionnaire in a randomized, controlled, non-inferiority trial at an ambulatory medical clinic, an ED, and a community-based organization in Providence evaluating the efficacy of the video vs. comparable orally-delivered information from an HIV test counselor (a RA) in regards to short-term HIV/AIDS and HIV testing knowledge [21]. We enrolled 18–64-year-old primarily Spanish-speakers (*n* = 150) in the trial. Randomization was stratified by health literacy level (lower vs. higher) as measured by the Short Assessment of Health Literacy-Spanish and English (SAHL-S&E), which has strong psychometric properties in assessing health literacy [22]. After the video or orally-delivered information, HIV/AIDS and HIV testing knowledge applicable to CDC recommendations was assessed through audio-computer self-interviews (ACASI) using our previously developed 25-item questionnaire. Of the 150 participants, 39% met criteria for lower health literacy. For all participants, the mean scores for correct items on the questionnaire for the video (20.4; 95% CI: 19.5~ 21.3) and orally-delivered information (20.6; 95% CI: 19.7~ 21.5) groups (Δ = − 0.15; 95% CI: -1.4~ 1.1) were similar, satisfying the a priori non-inferiority criterion. Of those who watched the video, 93% stated that they were well or very well informed, and of those who received information orally, 96% stated that they were well or very well informed. Mean knowledge scores among lower health literacy participants were similar (18.3 [video] vs. 19.6 [in-person]; *p* < 0.30). In multivariable linear regression analyses, lower mean knowledge scores were related only to health literacy level (β − 2.4; 95% CI: -3.8, − 1.1), and not demographic characteristics (age, gender, race, insurance status, years of formal education, nativity, US acculturation), study arm (video or in-person information), study location (ambulatory medicine clinic, ED, or community-based organization) or prior HIV testing.

Following the trial, we made minor improvements to the video based on the results of the study (e.g., clarifying areas for which study participants scored less well). We also translated the Spanish version into English (“What do you know about HIV and HIV testing?”). Afterwards, we conducted a brief pilot study at the Rhode Island Hospital ED verifying short-term improvement in HIV/AIDS and HIV testing knowledge as measured by our 25-item HIV/AIDS and HIV testing knowledge questionnaire. Using a within-subjects comparison (i.e., pre- vs. post-vide0), short-term HIV/AIDS and HIV testing knowledge improved for both English and Spanish speakers (English: 22.8 vs. 17.9, Δ 4.89; *p* < 0.01; Spanish: 19.9 vs. 16.1, Δ 3.73; *p* < 0.001). Yet, overall testing knowledge was lower and improvement in knowledge was less among Spanish- than English-speakers.

Despite the data supporting the use of videos for delivering HIV/AIDS and HIV testing information in EDs, this communication medium has multiple disadvantages. Videos require electronic equipment; can be time consuming to watch; are more expensive (relative to brochures) to produce, update, and adapt for multiple cultures and languages; and might be “information overload” and off-putting for some patients, particularly those with higher health literacy and repeat HIV testers.

In contrast to videos, pictorial brochures have fewer disadvantages and are a promising alternative to videos. Similar to videos, pictorial brochures combine text and graphics to help illustrate concepts and might be better than text-only brochures for lower health and general literacy persons [23]. Pictorial brochures share the advantage of text-only brochures in ease of delivery, no training required to provide them, ability to be mass produced in multiple languages, and lower expense. However, we know of no published study evaluating pictorial brochures for delivering HIV/AIDS and HIV testing information, or studies comparing pictorial brochures to videos on this topic.

In summary, there currently exists a state of equipoise regarding optimal HIV/AIDS and HIV testing information delivery modes in EDs in light of CDC’s recommendations: (1) videos have been shown to be as efficacious as orally-delivered information; (2) informational brochures have not been adequately studied, although they are currently recommended; and (3) there have been no published studies evaluating pictorial brochures for HIV testing.

Although it is reasonable to assume that delivery of HIV/AIDS and HIV testing knowledge should be tailored to meet the needs of the estimated 15–40% of ED patients with lower health literacy [24–27], there is no published research on this topic. In particular, we do not know if pictorial brochures and videos are equivalently efficacious modes of delivering HIV/AIDS and HIV testing information, or if one mode is better than the other and should be preferred. Also unknown is how delivery mode affects retention of HIV/AIDS and HIV testing knowledge over time. Prior research indicates that intensive interventions [28–32] lead to retained HIV/AIDS and HIV testing knowledge. However, there have been no studies evaluating retention of knowledge from less intensive—yet much more likely to be used—modes of information delivery (e.g., brochures, videos*)*. Because previously studied intensive interventions (e.g., multiple skill-building sessions, peer counseling) are impractical in the ED setting, shorter, easier-to-deliver, yet efficacious modes are needed. In addition, it is important for maintain the operational efficiency of EDs to know if, when, how, and for whom information needs to be provided for HIV re-testing.

Information is believed to be necessary but not sufficient as a stand-alone component of HIV-related behavior change [33]. Although the videos we created address HIV- and HIV testing-related motivation and behavioral skills commensurate with the Information-Motivation-Behavioral Skills (IMB) model [34, 35], their impact on HIV test seeking behavior, utilization/acceptance of repeat HIV testing, and engaging in HIV risk-taking behaviors remains unknown. Furthermore, no studies have examined HIV re-testing after ED-based testing, and few non-ED studies have investigated factors associated with acceptance of HIV re-testing [36–39]. Understanding reported reasons for accepting or declining HIV re-testing is important for guiding future HIV re-testing interventions and approaches as well as addressing testing barriers. If HIV/AIDS and HIV testing information, and more specifically how it is delivered (pictorial brochure vs. video, according to health literacy level and language), impacts HIV re-testing behaviors, there would be better justification for providing this information and more attention on how (and to whom) it should be delivered.

If HIV/AIDS and HIV testing information delivery in EDs must be matched to patient health literacy, efficient and accurate ways to identify lower health literacy ED patients also need to be identified. Identifying adult ED patients with lower health literacy remains a challenge partly due to two limitations. First, there is limited research demonstrating the accuracy of extant screening instruments in EDs. Second, there are challenges in applying the screening instruments that have been demonstrated to be valid and reliable in identifying lower health literacy ED patients. The ideal health literacy instrument will be reliable and valid, brief, and easy-to-administer at the point of need in EDs.

A set of three questions that might fit these qualifications previously was derived from the Short Test of Functional Health Literacy in Adults (S-TOFHLA)), a longer, well-established screening device. These three questions address patient self-assessed health literacy skills according to three aspects: (1) need for help reading, (2) confidence with understanding, and (3) problems with reading medical forms [40–43]. Research conducted in hospital and outpatient settings assessing the utility of these three questions is promising. However, they have not been tested in ED populations, which can have greater diversity of demographic characteristics. Further, they only have been examined among English speakers, which further reduces their use in US EDs. In contrast, the SAHL-S&E [22] can distinguish between English- as well as Spanish-speakers with higher or lower health literacy. However, the SAHL-S&E comprises 18 questions, requires equipment (flash cards, data recorder, calculations), and must be administered by trained staff. This instrument is useful for research, but more difficult to use in routine ED practice. A short, easy-to-administer efficacious health literacy screening instrument could be used by ED staff to identify patients needing a particular mode of information delivery (e.g., video, pictorial brochure) to improve and retain HIV/AIDS and HIV testing knowledge.

### The current research

In our ongoing study (“Facilitating HIV/AIDS and HIV Testing Literacy for Emergency Department Patients”), we are conducting a multi-site, randomized, controlled, longitudinal trial with 600 English- and 600 Spanish-speaking 18–64-year-old ED patients. Our sample will be stratified by language (English or Spanish) and by health literacy level (lower vs. higher) assessed with the SAHL-S&E [22]. Participants will be randomly assigned within health literacy level to receive HIV/AIDS and HIV testing information by video or a pictorial brochure.

The video and pictorial brochure are designed to increase HIV testing knowledge, motivation, and behavioral skills and influence HIV re-testing behaviors. We will assess short-term (in ED) improvement in HIV/AIDS and HIV testing knowledge [21] and its longer-term retention over 12 months. At 12-months post-enrollment, we will offer participants the opportunity to be retested for HIV and we will measure differential testing uptake as a function of information delivery mode, language, and health literacy level. In addition, using the IMB model [34, 35] as a heuristic framework, we will examine IMB model study-relevant constructs and their interrelationships, their impact on HIV re-testing behavior, and moderation of information delivery mode, language and health literacy.

The innovative design of this study will permit us to determine, with adequate power, if pictorial brochures and videos are equivalently efficacious in improving and maintaining retention of HIV/AIDS and HIV testing knowledge, regardless of health literacy level and language preference. It will also allow us to determine if one mode of information delivery is superior or inferior, and under what circumstances (e.g., health literacy level and language) they are superior or inferior. The unique design will also permit a determination if, and for whom, HIV/AIDS and HIV testing information should be tailored. It also allows assessment of the impact of information delivery mode, language, and health literacy on acceptance of HIV re-testing. The findings will inform EDs whether information delivery modes should be selected for patients by language and/or health literacy level, or if either mode is preferred. The results will also tell EDs if, when, how, and for whom information should be provided for those re-testing for HIV within 1 year.

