### Primary aims: HIV/AIDS and HIV testing knowledge acquisition and retention (information)

Determine how (Aim 1) short-term improvement and (Aim 2) longer-term retention of HIV/AIDS and HIV testing knowledge varies by information delivery mode (pictorial brochure or video), language (English or Spanish) and health literacy level (lower or higher) per four alternative hypotheses (HAs) (also provided are examples of outcomes of each HA):HA1 (3-way interaction of information delivery mode, language, and health literacy): e.g., improvement and/or retention of knowledge will be greatest among participants in the video arm who are English speakers and have higher health literacy, and will be least among those in the pictorial brochure arm who are Spanish speakers and have lower health literacyHA2 (2-way interaction of information delivery mode with language or health literacy): e.g., improvement and/or retention of knowledge will be greatest among participants in the video arm who are English speakers or higher health literacy patients, and will be least among those in the pictorial brochure arm who are Spanish speakers or lower health literacy patientsHA3 (no interaction with information delivery mode): e.g., improvement and/or retention of knowledge will be greater in the video arm than the pictorial brochure arm regardless of language and health literacy levelHA4 (no difference): improvement and/or retention of knowledge will be the same regardless of information delivery mode, language, and health literacy level (i.e., either a pictorial brochure or a video is useful for all patients)

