#### Sample size considerations

The study sample size is *n* = 1200, with equal size strata (*n* = 150) by language, health literacy level, and information delivery mode (Fig. 4). This sample size is based on a 2x2x2 full factorial design and will satisfy the requirements for analysis of the two primary aims and the four alternative hypotheses paired with each aim. The minimum sample size is calculated for a power of 0.80 and a two-sided *α = 0.05* level of significance (Table 3). In general, a larger sample size is needed for greater variation of scores within study arms and strata, lower within-person correlations of scores, and higher loss-to-follow-up. To maximize power, we chose conservative values based upon our prior studies. We increased the sample size by 20% to account for the heterogeneity in patients among the four study sites, and by a conservative additional 25% to account for possible attrition. Based upon other 12-month ED intervention follow-up studies [10], HIV/STD testing studies [57–59], and studies conducted at our own ED [60, 61], a 25% attrition rate at 12 months likely is a worst-case scenario. We expect that our experience and enhanced measures to encourage and facilitate follow-up will result in higher follow-up rates. As of publication of this manuscript, 1165 participants enrolled completed the three-month follow-up.

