**Fig. 4 Fig4:**

Sample size by study arm, language, and health literacy level

**Table 3 Tab3:** Sample size rationale by primary aims

Primary Aims	Minimum sample by stratum	Total minimum sample	Rationale and assumptions for minimum sample sizes and final sample sizes for each primary aim
Aim 1. Short-term improvement in HIV/AIDS and HIV testing knowledge ** HA1**: 3-way interaction (mode*language*literacy level) ** HA2**: 2-way interaction (mode*language or literacy level) ** HA3**: no interaction (difference by mode only) ** HA4**: no difference	**125** This **minimum** sample size by stratum will yield a power of 0.80, 0.97 and 0.99 for testing HA1, HA2, HA3 versus HA4 (HA4 as the NULL) Final sample per stratum (information delivery mode, language, and health literacy level) is 150	**1000** The **final sample** after adding 20% to account for the heterogeneity in patients among study sites is **1200** = 1000*(1 + 20%)	• Based on our prior video studies [17, 19, 21], we assume that the scores on the 25-item questionnaire is a normal distribution with a standard deviation of ~ 3 • Before information delivery, mean scores of the two arms are assumed to be the same (due to random assignment) per stratum • Short-term within-person correlation is 0.7 or higher [21] • The pictorial brochure will improve knowledge by an average of 2 points. The video will improve the knowledge by an average of 3.5 points. The effect size is Δ = 3.5–2 = 1.5. (HA3) • 2-way intrxn (mode*language or literacy level) effect size is Δ = 1.5 + 0.75 = 2.25. (HA2), e.g. for those speaking English OR with high health literacy • 3-way intrxn (mode*language*literacy level) effect size is Δ = 1.5 + 0.75 + 0.75 = 3.0, e.g. for those speaking English AND having high literacy AND watching the video

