### Study analysis (begins at end of recruitment month 43)

#### Enrollment summary and comparison of participants at baseline

We will report on participant enrollment and summarize the reasons for accepting or declining enrollment or drop-out from the study using the Consolidated Standards of Reporting Trials (CONSORT) approach [62]. We will summarize the demographic characteristics, HIV testing history, and health literacy level (measured by the SAHL-S&E [22] and brief instruments) using conventional statistics, such as means/standard deviations, medians/ranges, or counts/frequencies with corresponding 95% confidence intervals (CIs), as appropriate. For Latino participants, we will summarize nativity and US acculturation (measured by the SASH [63, 64]) in a similar manner. We will summarize these baseline characteristics for all participants and as stratified by informational delivery mode (pictorial brochure or video), language preference (English or Spanish), and health literacy level (lower or higher). Next, we will compare the baseline characteristics of study participants between the study arms using Pearson’s Χ^2^ or Fisher’s exact test for categorical variables and Student’s t-test for normally distributed or Wilcoxon’s rank-sum test for non-normally distributed continuous variables to assess the success of the randomization procedure. Any chance imbalances between the two arms will be documented and investigated, and will be adjusted for by including the imbalanced covariate as an independent variable in our subsequent regression analyses, or through a weighted analysis using a propensity score (propensity to be enrolled in the study with weights equal to the inverse of the propensity score) [65]. A two-tailed, *α = 0.05* significance level will be used for all analyses.

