If a linear assumption is supported by data, the linear predictor in the above model will be expressed as *α*_*0*_ *+ β*_*1*_*[time] + β*_*2*_*[time]*R*_*i*_*[mode]*, where *β*_*1*_ and *β*_*2*_ capture HIV/AIDS and HIV testing knowledge retention rate over time and the difference in the rate between two delivery modes. We will further evaluate the 2- and 3-way interactions *β*_*2*_*[time]*[language]*R*_*i*_
*[mode]* and *β*_*2*_*[time]*[health literacy level]*R*_*i*_*[mode]* and possibly (if data allow) 4-way interactions *β*_*2*_*[time]*[language]*[health literacy level]*R*_*i*_*[mode]*, to investigate the interaction of information delivery mode with language and health literacy and whether one delivery model works better in certain sub-groups. Our analysis by time will permit us to determine if and when HIV/AIDS and HIV testing knowledge degrades, and if and when knowledge reaches baseline pre-information levels (i.e., before an intervention), which would suggest a need for repeat delivery of this information at subsequent HIV testing encounters within 12 months. We also will determine if degradation varies by information delivery mode, language, and health literacy level. We recognized that there is no established minimum standard for what level of HIV/AIDS and HIV testing knowledge is necessary or desired; however, we believe that it should be at least greater than pre-information knowledge levels, and will plan the analyses accordingly.

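### Adequate power is claimed for equivalence of brochure and video, but all stated power is for detecting differences, and no equivalence margin or confidence-interval rule is given

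*Protocol article*

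**What the plan says.** The section The current research makes the promise that the design can determine, with adequate power, "if pictorial brochures and videos are equivalently efficacious in improving and maintaining retention of HIV/AIDS and HIV testing knowledge". It covers both improvement and retention, and is meant to hold whatever the patient's literacy or language. Superiority and inferiority are promised separately, in the sentence that follows.

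The Primary aims section lists four alternative hypotheses. HA4 is that "improvement and/or retention of knowledge will be the same regardless of information delivery mode, language, and health literacy level", and it is glossed as meaning that either mode serves every patient.

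Sample size considerations says that the 2x2x2 design meets the needs of both primary aims and all four hypotheses. It also says: "The minimum sample size is calculated for a power of 0.80 and a two-sided" 0.05 level. Table 3 gives the basis for Aim 1: the minimum "sample size by stratum will yield a power of 0.80, 0.97 and 0.99 for testing HA1, HA2, HA3 versus HA4 (HA4 as the NULL"). The Aim 2 row repeats the three powers with the same null.

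For the analysis, a two-tailed 0.05 "significance level will be used for all analyses". The primary aims analysis consists of t-tests or signed-rank tests, MANOVA/ANCOVA and mixed models, with interest in the mode coefficient and its interactions. It gives no tolerance for sameness and concedes that "there is no established minimum standard for what level of HIV/AIDS and HIV testing knowledge is necessary or desired". The only non-inferiority criteria in the article belong to the group's earlier trials of video against oral information.

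**The concern.** A test of HA1, HA2 or HA3 against HA4 can reject HA4. Failing to reject it is not evidence that the modes are the same, because an imprecise comparison fails to reject easily. High power against a 1.5-point difference is also not power to show that the difference is negligible. That second power cannot be defined until someone says how small is negligible.

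The article says that its results will guide how emergency departments deliver this information, and it describes brochures as cheaper and easier to deliver than videos. A statement that either mode will do is therefore one of the practical outputs. If it rested on non-significance alone, readers could not tell a demonstrated similarity from a wide interval, particularly for 12-month retention within subgroups.

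**Working it through.** **Inputs (Table 3 and Sample size considerations).** Score SD about 3; within-person correlation 0.7 (Aim 1) and 0.4 (Aim 2); 150 per cell in 8 cells; 25% attrition for Aim 2. The planning difference between modes is 1.5 points for Aim 1 and 2.5 for Aim 2. The equivalence margin is not given, so a range is shown.

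**The plan's own figures.**
- Totals: 1000 × 1.20 = 1200, and 800 × 1.25 × 1.20 = 1200. Both agree.
- Aim 1 power at 125 per cell is Φ(Δ/SE − 1.96), with SE = SD√(8/125) for the three-way contrast, SD√(4/250) for the pooled two-way contrast and SD√(2/500) for the pooled mode effect.
- With Δ = 3.0, 2.25 and 1.5 and no credit for correlation (SD 3√2 = 4.24), the SEs are 1.073, 0.537 and 0.268. The powers are 0.80, 0.99 and >0.99, close to the stated 0.80, 0.97 and 0.99. The article does not spell out this variant; using the stated correlation of 0.7 instead gives >0.99 for all three.
- On either reading, each figure is the probability of rejecting HA4.

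**What the same sample offers for equivalence of the modes.**
- SD of change = 3√(2(1−ρ)): 2.32 for Aim 1 and 3.29 for Aim 2.
- SE of the mode difference = SD√(2/n per arm).
- Power of two one-sided 5% tests (TOST) at zero true difference = 2Φ(M/SE − 1.645) − 1, where M is the margin.
- Smallest margin with 80% power = (1.645 + 1.282) × SE.

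| Comparison | n per arm | SE | Power at M = 0.5 / 0.75 / 1.0 / 1.5 | Smallest M for 80% |
|---|---|---|---|---|
| Aim 1, pooled | 600 | 0.134 | 0.96 / >0.99 / >0.99 / >0.99 | 0.39 |
| Aim 1, one language-by-literacy stratum | 150 | 0.268 | 0.17 / 0.75 / 0.96 / >0.99 | 0.79 |
| Aim 2 at 12 months, pooled | 450 | 0.219 | 0.48 / 0.93 / >0.99 / >0.99 | 0.64 |
| Aim 2, one language or one literacy level | 225 | 0.310 | 0 / 0.56 / 0.89 / >0.99 | 0.91 |
| Aim 2, one language-by-literacy stratum | 112.5 | 0.438 | 0 / 0.05 / 0.48 / 0.93 | 1.28 |

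The Aim 2 rows are a worst case: full 25% loss, the lowest stated correlation and a raw change score. With baseline adjustment the SD is 3√(1 − 0.4²) = 2.75. The stratum SE is then 2.75√(2/112.5) = 0.367, and the smallest margin is 2.927 × 0.367 = 1.07.

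**How often a true 1-point difference at 12 months is non-significant**, from Φ(1.96 − 1/SE):
- one stratum, raw change: 37%
- one stratum, baseline-adjusted: 22%
- pooled, raw change: about 0.5%

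**The case against.** The article says determine if, not determine that, and nowhere states that p > 0.05 will be read as equivalence. Using HA4 as the null is the ordinary set-up for a factorial trial powered on differences. The interpretation of a null result could be left to an analysis plan, and this group has used prior non-inferiority criteria before. All of that is fair, and it means that a misreading of a null result cannot be presumed. It does not rescue the power claim, because the article itself fixes the power basis, the role of HA4 and the tests.

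Two stronger readings are tempting and are not supported:

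- **A reader might infer that the trial would wrongly conclude HA4 more than a third of the time.** The 37% is the miss rate of one t-test in one of four strata under worst-case assumptions. HA4 is a statement about all patients. If the difference were 1 point throughout, the pooled 12-month contrast would miss it about 0.5% of the time. The article calls 25% attrition a likely worst case and reports that 1165 participants had completed the 3-month follow-up.
- **A reader might infer that 1200 is too few to show equivalence.** That depends on a margin that the documents do not give. The pooled comparisons support quite tight margins.

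It is also right that a CI for the mode difference cannot establish HA4 as written, since HA4 further requires no difference by language or literacy. Nor is it cheap to demand equivalence at every level. With an assumed margin of 0.75, the pooled 90% CI and the four CIs by language and by literacy level would all fall inside for 12-month retention only about 17% of the time (by simulation, raw change score) even at zero true difference.

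**Conclusion.** The point stands as a mismatch between claim and plan. Adequate power to determine equivalence is asserted, but the plan has no margin, no equivalence test or CI rule, and no power figure for that conclusion. A non-significant difference is the only route it offers to HA4.

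No planned difference test and no sample size is shown to be wrong by this. What the sample can support runs from margins of about 0.39 points (Aim 1) and 0.64 points (12-month retention) for the pooled mode effect, to about 0.79 and 1.28 within a language-by-literacy stratum (about 1.07 for retention if baseline-adjusted). These figures rest on the article's SD and correlations, normal approximations, zero true difference and, for Aim 2, the full 25% loss. The claim that equivalence can be determined whatever the literacy or language is therefore least secure for retention by stratum, where it would need a margin not far below the 1.5-point difference that the trial was planned to detect.

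**What to change.** Separate equivalence of the two modes from HA4. Before any analysis by arm, state and justify a margin on the 25-item score that is smaller than the 1.5-point planning effect. For each aim, conclude overall mode equivalence only if the 90% CI for the pooled, baseline-adjusted mode difference lies wholly inside the margin, and give the power for that rule.

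Report mode differences by language, literacy level and stratum with CIs, and call them inconclusive where the CI crosses the margin. Make no stratum-level equivalence claim for retention unless the chosen margin supports it.

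If no margin can be defended, delete the claim of adequate power for equivalence in The current research, and report HA4 as no difference detected, with CIs.

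No new data are needed. The cost is the work of justifying a margin where the article says that no knowledge standard exists, and accepting that some results, mainly retention by subgroup, will be inconclusive.
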